## Methods

### Overview of the *Suubi+Adherence* Study (original study)

The goal of *the Suubi+Adherence* study was to examine the impact and cost of an innovative EE intervention to increase adherence to HIV treatment for HIV-infected youth (see Suubi+Adherence study protocol [3] for more details). The study was guided by asset-theory [15, 16] and tested a FEE intervention consisting of an incentivized youth financial savings accounts (YSA) augmented with peer mentorship, financial literacy training (FLT) and income generating activities (IGAs) for poverty-impacted youth living with HIV and their families. The intervention was intended to: 1) economically stabilize families to yield sufficient income to meet the needs of managing HIV as a chronic illness (e.g. having sufficient nutritional resources, and funds to cover costs associated with medical care and; 2) provide support for adherence to antiretroviral therapy (ART).

*The Suubi+Adherence* study recruited 702 YLHIV. Inclusion criteria included: 1) tested positive for HIV (confirmed by medical report and aware of status); 2) living within a family; 3) being 10–16 years of age (at enrolment); 4) having been prescribed ART; and 5) enrolled in ART care at one of the 39 health clinics/centers in the greater Masaka Region of Uganda -a geographical region hardest hit by HIV/AIDS (prevalence 10.6% vs. 7.2% national average) [131–133]. Health clinics were eligible if they: 1) had existing procedures tailored to adolescent adherence (including adolescent-specific clinic days and peer counselling) and 2) were accredited by the Uganda Ministry of Health as a provider of ART within the study districts.

Following enrolment and baseline assessments, 39 participating clinics were randomly assigned to one of two study groups, resulting in 19 clinics (n = 344 participants) assigned to the control condition and 20 clinics (n = 358 participants) assigned to the intervention condition. A two-arm, cluster randomized trial design was employed where all participants attending the same clinic were assigned to the same study group. All participants received medical Standard of Care (SOC), as defined by the Uganda Ministry of Health guidelines for pediatric and adolescent HIV care and treatment; and psychosocial SOC, consisting of information leaflets on adherence and support provided by lay counsellors including persons living with HIV who have been trained in ART adherence counselling, known as “expert clients”. Due to inconsistency in which SOC is often provided in the region, *Suubi+Adherence* provided youth in both study conditions with a bolstered standard of care (BSOC), which included eight information sessions on adherence to ART, adapting evidence-based, print cartoons to portray adherence topics in a relatable manner [134]. Adolescents in the intervention group received the BSOC as well as a FEE intervention consisting of a Youth Savings Account (YSA), matched at a rate of 1:1 and from which financial savings could be used for medical expenses, family microenterprise development or education related expenses (including school lunches and fees). As part of the YSA package, the intervention group also received four workshops blending FLT and life skills with topics on asset building, IGA, goal setting, and risk mitigation. Data was collected at baseline, 12, 24, 36 and 48- months post-intervention initiation. The study retention rate of 93.4% over a 6-year period (2012-2018).

### Current study

This study will examine the longitudinal HIV antiretroviral therapy (ART) adherence and related outcomes, as well as the potential mechanisms of protective health behaviors among youth living with HIV (YLHIV) who participated in an evidence-based family economic empowerment (FEE) intervention in rural Uganda and are now transitioning into young adulthood (see figure 1).

**Fig. 1 Fig1:**
[figure not shown]
Suubi+Adherence-R2 Conceptual Framework

The research team will rely on the completed future contact forms of the *Suubi+Adherence* participants and the community trust, including with the health clinics and Masaka Diocese, for tracking and following the *Suubi+Adherence-R2* participants. The future contact information completed at the time of enrollment provides the ability to contact them, even if they have moved. Participants will be followed up within their original study conditions. For treatment group participants, we will request their bank statements each quarter to ascertain their savings. No additional matching will be done.

### Inclusion Criteria

All participants in the *Suubi+Adherence* study will be eligible for re-consenting and re-enrollment into the Suubi+*Adherence-R2* study and followed for an additional 5-year period. A recent follow-up with the 39 clinics (December 2019) by Washington University’s International Center for Child Health and Development (ICHAD) office in Uganda confirmed that with conservative estimates, we will locate at least 80% of the original sample. Following reconsenting, participants will be interviewed for 5 years, once a year. Figure 2 provides the timeline.

**Fig. 2 Fig2:**
[figure not shown]
Suubi+Adherence and Suubi+Adherence-R2 Follow-up Timeline

### Ethics and Informed Consent

The study received approval from the Institutional Review Board (IRB) at Washington University in St. Louis (IRB # 201704066) and the in-country local IRBs in Uganda: Makerere University School of Public Health Review Committee (Protocol # 210), and Uganda National Council of Science and Technology (UNCST, SS 2969). All potential amendments to the study protocol will be submitted for approval to the above-mentioned IRBs by the MPIs.

Written informed consent will be obtained from all participants. They will be assured that participation is voluntary and medical care will not be affected. Procedures for confidentiality, including handling of data, Certificates of Confidentiality, and HIPAA will be explained. Recruitment and consent procedures are all based on successful procedures from Suubi+Adherence. Since all participants will be 18 or older, we will not need caregiver consent to participate in Suubi+*Adherence-R2*.

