A recent HIV assessment in Uganda, a poor SSA country hardest hit with HIV, puts the prevalence of viral load suppression among adolescents and young adults (15 to 24 years old) to be 44.9% for females and 32.5% for males [2]. For six years (2012-2018), the *Suubi+Adherence* study team prospectively followed 702 YLHIV (aged 10 to 16 years at enrollment) randomized to two study arms across 39 clinics in Uganda: 1) control arm consisting of bolstered standard of care (BSOC) and 2) intervention arm consisting of BSOC and a FEE intervention comprising an incentivized youth financial savings account (YSA) augmented with financial literacy training (FLT) and peer mentorship (see Suubi+Adherence protocol paper [3] for more details). Our study findings pointed to superior short-term viral suppression and positive child health and mental health functioning among the intervention arm receiving the FEE intervention compared to the control arm [3–6]. The *Suubi+Adherence-Round 2* study will examine whether the results are maintained through young adulthood, an incredibly vulnerable transition period [8], particularly in areas of cognitive development, mental health, sexual risk taking behaviors and alcohol/drug misuse [9–12]. Moreover, given the stigma of HIV, YLHIV report lower social support, and increased risk for non-adherence as they become more autonomous [13, 14].

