### Sample Tracking, Retention and Attrition

The *Suubi+Adherence* study (2012-2018) had an attrition rate of 6.6%, leaving a total study sample of 656 – by study end (December 2018). These numbers reflect: a) the study being implemented in a stable region with low geographical moves; b) trust of the study team by the community members. This trust has been built and/nurtured over a 15+ year period that [name] (Lead PI) and his colleagues have been engaged in the greater Masaka region and the surrounding districts; c) Washington University has a fully-fledged field office (ICHAD) in the Masaka region allowing for easy engagement between the study team and the local collaborators; and d) the study team has a well-established tracking system implemented by ICHAD resulting in very low attrition rates—as reflected in Table 1 below, detailing actual retention rates from the *Suubi+Adherence* original study.

**Table 1 Tab1:** Suubi+Adherence Retention rates: (2012-2018) [48, 49, 135]

Baseline/Wave 1	Wave 2	Wave 3	Wave 4	Wave 5
*N*=702	*N*=670, retention rate=95.4% (lost to follow-up *n*=32)	*N*=663, retention rate=94.4% (lost to follow-up *n*=39)	*N*=662, retention rate=94.3% (lost to follow-up *n*=40)	*N*=656, retention rate=93.4% (lost to follow-up *n*=46)

During re-consenting, we will ask participants to update their future contact information with updated telephone number(s) (if they have one: 95% of participants reported having access to a phone in the household), and an updated list of the names, and contact information of three people who will always know how to reach them. Participants will be reminded that if we contact the people listed, we will not discuss any details about them or their study participation. Like we have done in the past, we will use these records solely to help track their location and only if we have lost contact. We have effectively used these procedures in our previous research studies, resulting in very low attrition rates. Thus, we conservatively expect to re-consent at least 80% of the 702 participants (N=562) for the Suubi+*Adherence-R2* study. We expect attrition from reconsented cohort (wave 6, in 2020) to the end of the follow-up period (wave 10 in 2025) to be no more than 20%. (See Table 1 above).

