All requests, current and future, to use the data are reviewed by the MPIs. Any data files that are provided to other individuals are stripped of identifiers and contain only code numbers so that data across multiple assessment waves can be matched. Within the informed consent/assent, participants are notified of the above procedures.

The MPIs ([name], [name], [name]) and Project Coordinator in Uganda are social workers by training. They will all be available to talk to the participants who may experience discomfort with the questions on the interviews, should they cause concern. [name] and the Mildmay team are medically trained and will be able to talk to participants who may experience discomfort during blood draw. In case further counseling is needed, the project staff will make the referrals.

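### Caregiver consent is dropped because everyone is said to be at least 18 at re-consent, but the article's own ages and dates do not support that

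*Protocol article*

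**What the plan says.** The Ethics and Informed Consent section of the protocol article makes an unconditional statement of fact and draws a procedure from it: "Since all participants will be 18 or older, we will not need caregiver consent to participate in" Round 2. No procedure is given for a participant who turns out to be younger.

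Four other places bear on whether the statement is true:

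- **Age at entry.** The overview of the original study lists "being 10–16 years of age (at enrolment") among its inclusion criteria. The Background agrees: "aged 10 to 16 years at enrollment) randomized to two study arms across 39 clinics in Uganda".
- **Who may enter Round 2.** Under Inclusion Criteria, all original participants "will be eligible for re-consenting and re-enrollment into the" new study. There is no age floor and no rule to wait until a participant is 18.
- **Original schedule.** "Data was collected at baseline, 12, 24, 36 and 48- months post-intervention initiation". The article dates the study as a whole ("For six years (2012-2018), the" study team followed the cohort), and Sample Tracking, Retention and Attrition gives a sample of 656 "by study end (December 2018").
- **Re-consent.** The same section places wave 6 in 2020.

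**The concern.** The oldest child at entry is an adult by 2020 on any reading. The statement has to hold for the youngest, and a 10-year-old needs eight years. The original study began in 2012, so the eight years are available only to children enrolled in its first year, and in full only if their own re-consent comes late enough in 2020.

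The stakes are mainly protective. Table 2 schedules viral load, sexual risk behaviour and substance misuse at the re-consent time point, and the Biological assay section starts STI testing, including vaginal swabs, at wave 6. If the text is followed as written, anyone still under 18 would go through these procedures with no caregiver-permission route. If staff instead turn such a person away, the loss falls only on the youngest participants. That is selective attrition, which the article's plan to re-consent 80% of the 702 does not consider.

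**Working it through.** **Inputs from the article**

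- Youngest age at enrolment: 10 (Background; overview of the original study).
- Original study period: 2012 to 2018, ending December 2018 (Background; Sample Tracking, Retention and Attrition).
- Last original visit, Wave 5: 48 months after intervention initiation (overview of the original study; Table 1).
- Re-consent, wave 6: 2020 (Sample Tracking, Retention and Attrition).

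**Not given:** calendar dates of enrolment, the month of re-consent and the age distribution. Enrolment is therefore varied from January 2012 (earliest start of the stated period) to the end of December 2014. The later bound is December 2018 minus 48 months. Strictly, it bounds intervention initiation.

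**Step 1. When does the stated minimum of 18 hold?** Youngest age at re-consent = 10 + (re-consent date − enrolment date). Setting this to at least 18 requires an enrolment date no later than the re-consent date minus 8 years:

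- re-consent January 2020: enrolled by January 2012
- re-consent mid-2020: enrolled by mid-2012
- re-consent December 2020: enrolled by December 2012

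So the stated minimum can be reproduced, but only for enrolment within 2012.

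**Step 2. Youngest possible age over the permitted dates** (child enrolled at exactly 10.0):

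| Enrolled | Re-consent January 2020 | Re-consent mid-2020 | Re-consent end 2020 | 48 months after enrolment |
|---|---|---|---|---|
| January 2012 | 18.0 | 18.5 | 19.0 | January 2016 |
| Mid-2012 | 17.5 | 18.0 | 18.5 | mid-2016 |
| January 2013 | 17.0 | 17.5 | just under 18 | January 2017 |
| January 2014 | 16.0 | 16.5 | just under 17 | January 2018 |
| End of 2014 | 15.0 | 15.5 | 16.0 | end of 2018 |

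From January 2013 on, a child enrolled at exactly 10 is under 18 at every re-consent date in 2020.

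**Step 3. Which enrolment dates do the other passages suggest?**

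- The 656 given for study end in December 2018 is the Wave 5 count in Table 1 (656/702 = 93.4%, which matches the stated retention). Wave 5 is the 48-month visit. If everyone had enrolled in 2012 and started soon after, Wave 5 would have fallen in 2016, about two years or more before study end.
- The Data collection section says the original assessments were 12 months apart. Five such assessments span four years. Keeping enrolment in 2012 with a Wave 5 near December 2018 would need a gap of about two years between enrolment and initiation (December 2012 to December 2014).
- The Discussion describes the combined dataset as covering ten years, and follow-up ends in 2025: 2025 − 10 = 2015. This may be loose rounding and carries little weight, but it too does not point to 2012.

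Together these favour at least some enrolment after 2012. None of them states a date.

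**The case against.** The strongest reply is that the contradiction is inferred. The article prints no enrolment dates. Its only explicit period is 2012 to 2018, and it reports 93.4% retention over six years. Read literally, that puts baseline in 2012, and 10 + 8 = 18 in 2020. Visits are timed from intervention initiation, whereas age is fixed at enrolment, which came before the clinics were randomised, so counting back 48 months does not strictly date enrolment. Figure 2, the timeline for both studies, is not shown and may settle the matter. The named review boards have approved the study.

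Much of this stands. A 2012 enrolment for every young child cannot be excluded, so a reader should not infer that 16- and 17-year-olds are certainly in the cohort. Nor can a share or headcount of minors be supported, because that would need both an age distribution and enrolment months. The sentence "Within the informed consent/assent, participants are notified of the above procedures" might be read as showing that minors are expected. It sits among data-handling procedures that continue from the original study and may be carried-over wording, so it is weak evidence at most.

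The reply does not rescue the sentence itself. Six years of follow-up from baseline and a five-wave schedule ending at 48 months agree only if there was a long delay before initiation or a long close-out after Wave 5, and the article describes neither. Enrolment spread over 2012 to 2014 would reconcile them more simply, and then the statement could fail. Start-up time at the beginning of 2012 would push enrolment later still. That participants turn 18 during follow-up does not help either, because consent and the first battery come at wave 6.

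**Conclusion.** The concern holds in a limited form. The article waives caregiver consent on an unconditional age statement that its own enrolment ages, eligibility rule and dates do not support. The statement is true only at the early edge of the permitted dates, with every child near age 10 enrolled in 2012 and at least eight full years before re-consent. The 48-month Wave 5 count reported for December 2018 suggests later enrolment, in which case some participants could be under 18 at wave 6.

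The size can be given only as the youngest possible age: about 15 to 19, depending on enrolment between January 2012 and the end of 2014 and re-consent during 2020. The number under 18 cannot be computed, and its range includes zero. Nothing here changes the power figures. The point is more than a missing detail, because the rule as written leaves no protected route for a minor facing blood draws, STI tests and sensitive interviews.

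**What to change.** Replace the all-adult statement in Ethics and Informed Consent with a date-of-birth check for every participant at re-consent. For anyone under 18, specify a route that the approving ethics committees accept: caregiver permission with the participant's assent, or deferral of consent until the 18th birthday. State the calendar dates of original enrolment and the youngest age expected at wave 6, so that this section agrees with the overview of the original study, Inclusion Criteria, and Sample Tracking, Retention and Attrition. Keep a record of anyone deferred or not re-enrolled because of age, so that the attrition-bias checks already planned can take it into account.

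The cost is an amendment to the consent wording and committee approval. If the records show that everyone is 18, the check costs almost nothing. Deferral has a price in data: a participant aged 16.0 in January 2020 would wait two years and could miss two of the five annual assessments, whereas caregiver permission with assent would keep the full schedule. The choice belongs to the committees.

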### Sample Tracking, Retention and Attrition

The *Suubi+Adherence* study (2012-2018) had an attrition rate of 6.6%, leaving a total study sample of 656 – by study end (December 2018). These numbers reflect: a) the study being implemented in a stable region with low geographical moves; b) trust of the study team by the community members. This trust has been built and/nurtured over a 15+ year period that [name] (Lead PI) and his colleagues have been engaged in the greater Masaka region and the surrounding districts; c) Washington University has a fully-fledged field office (ICHAD) in the Masaka region allowing for easy engagement between the study team and the local collaborators; and d) the study team has a well-established tracking system implemented by ICHAD resulting in very low attrition rates—as reflected in Table 1 below, detailing actual retention rates from the *Suubi+Adherence* original study.

**Table 1 Tab1:** Suubi+Adherence Retention rates: (2012-2018) [48, 49, 135]

Baseline/Wave 1	Wave 2	Wave 3	Wave 4	Wave 5
*N*=702	*N*=670, retention rate=95.4% (lost to follow-up *n*=32)	*N*=663, retention rate=94.4% (lost to follow-up *n*=39)	*N*=662, retention rate=94.3% (lost to follow-up *n*=40)	*N*=656, retention rate=93.4% (lost to follow-up *n*=46)

During re-consenting, we will ask participants to update their future contact information with updated telephone number(s) (if they have one: 95% of participants reported having access to a phone in the household), and an updated list of the names, and contact information of three people who will always know how to reach them. Participants will be reminded that if we contact the people listed, we will not discuss any details about them or their study participation. Like we have done in the past, we will use these records solely to help track their location and only if we have lost contact. We have effectively used these procedures in our previous research studies, resulting in very low attrition rates. Thus, we conservatively expect to re-consent at least 80% of the 702 participants (N=562) for the Suubi+*Adherence-R2* study. We expect attrition from reconsented cohort (wave 6, in 2020) to the end of the follow-up period (wave 10 in 2025) to be no more than 20%. (See Table 1 above).

We will keep careful records of those who drop out of the study and test for attrition bias based on data we will have prior to participant drop-out. To the extent that such bias is present, we will limit generalizations accordingly, or, where possible, introduce statistical adjustments to address bias. These strategies follow the general protocol used in our earlier NIH funded studies in the study area [74, 96, 98, 102, 124–126, 136–139], including the 6-year *Suubi+Adherence* study [3] which yielded a high retention rate (93.4%) over a 6-year period, and other Suubi [140–144] and the Bridges studies (retention rate: 92.7% over 5 years) conducted by the team [125, 139, 145, 146]. Combined with the original *Suubi+Adherence, Suubi+Adherence-R2* will be one of the most complete longitudinal data sets on behavioral health in YLHIV within a FEE intervention framework. This will allow us to generate knowledge on the long-term impact of FEE interventions on YLHIV, especially during social transitions.

### Data collection

We will use self-report questionnaires with read-aloud procedures by staff to address issues of literacy. Multiple research assistants (RAs) will be hired by ICHAD to conduct assessments. To encourage truthful responding, we will remind participants that responses are confidential and re-explain to them the security system that makes it impossible to link a name to data. Each participant will complete five interviews, 12 months apart. We selected this frequency in consultation with the clinics, statisticians, and behavioral experts to balance the scientific value of capturing change through frequent interviews, with the needs of participants and clinics and with our concerns about burden, data quality, and attrition. The 12-month interval between assessments in the original *Suubi+Adherence* proved sufficiently short enough to capture critical information, but long enough to avoid response bias or problems with retention or participation.

The complete battery will be administered at all time-points and participants will be interviewed individually, which will last between 60-90 minutes. The battery takes into account: 1) sensitivity to participant’s literacy (RAs read questions aloud and help fill out measures); 2) need for trust and rapport, and 3) use of local phrases and terms. In our previous work, participants completed these interviews without incident [74, 96, 98, 102, 124–126, 136–139], often reporting positive experiences in being interviewed. If participants express distress or issues of confidentiality emerge, we have developed an emergency protocol successfully used in *Suubi+Adherence* and other ICHAD studies conducted in the region [3, 74, 96, 98, 102, 124–126, 136–139, 142–144]. All assessments will take place in ICHAD’s private research field offices in Masaka; at satellite sites: MildMay, RTY-Uganda (see Letters of Support); or at the participants’ homes (if they request it and there is sufficient privacy to ensure confidentiality. Flexibility in interview location has been critical to Suubi+Adherence and other ICHAD studies success to date, with approximately 40% conducted in research offices in Masaka, and 50% in satellite sites. All measures (Table 2) have been pre-tested in the *Suubi+Adherence* study and other ICHAD studies [5, 9, 32], and made culturally appropriate to the Ugandan context. The added cognitive tests have also been previously validated in Uganda with YLHIV [19, 20].

**Table 2 Tab2:** Suubi+Adherence-R2 Study Measures

Variable	Measurement	Reliability	Timepoint
Demographics (Respondent: Adolescent Participant)			
Age; sex (assigned at birth), orphan status (single vs. double); socioeconomic status; family composition/structure; caregiver educational level	Socio-demographic questionnaire	n/a	^a^T1-RC, 12, 24, 36, 48
Moderators (Respondent: Adolescent Participant)			
Rural/urban/semi-urban; exposure to outside HIV/STI-related programs; economic/household income; asset accumulation			^a^T1-RC, 12, 24, 36, 48
Potential Mechanisms of Change (Respondent: Adolescent Participant)			
Self-efficacy	Adapted Tennessee Self-Concept Scale [147] (TSC-2) (*pretested in Suubi Studies*)	0.81	^a^T1-RC, 12, 24, 36, 48
Education plans/aspirations	Adapted Monitoring the Future Survey [148]	n/a	^a^T1-RC, 12, 24, 36, 48
Motivation to participate	Questions tested in previous studies [103, 124, 149, 150]	n/a	^a^T1-RC, 12, 24, 36, 48
Family Support	Social Support Behaviors Scale (SS-B) [151]Family Cohesion Scale [152], Krauss Interview [153]Parent Child Relationship Inventory (PCRI) [154]	0.77 0.69 0.91	^a^T1-RC, 12, 24, 36, 48
Family Stability	Socio-demographic questionnaire	n/a	^a^T1-RC, 12, 24, 36, 48
Hopelessness	Beck Hopelessness Scale [152]	0.79	^a^T1-RC, 12, 24, 36, 48
Self-esteem	Rosenberg Self-Esteem Scale [155]	0.77-0.88	^a^T1-RC, 12, 24, 36, 48
Condom Negotiation Self-Efficacy	Condom negotiation self-efficacy scale [156]	0.80	^a^T1-RC, 12, 24, 36, 48
Sexual Communication Skills	Sexual Communication Scale [157]	0.80	^a^T1-RC, 12, 24, 36, 48
Transitions (education, employment, residential independence, prosocial transition, relationship/marital status, pregnancy/parenthood	Demographics, MTF, Work history interview, Relationship assessment scale, Adolescent Sexual Behavior Assessment (ASBA), additional prosocial activities		^a^T1-RC, 12, 24, 36, 48
Social Support	Multidimensional scale of perceived social support MSPSS [158]	0.84	^a^T1-RC, 12, 24, 36, 48
Access to services	RBA Services [159], Treatment Services Review (TSR) teen and adult versions [160–162]	.66-.83	^a^T1-RC, 12, 24, 36, 48
Cost of staff time, supplies, overhead for IDAs	Project records; Admin. Review	n/a	ongoing
Substance misuse	Questions adapted from PhenX Toolkit [163], Alcohol, Smoking, and Substance Involvement Screening Test [164], DISC-IV modules, CIDI modules	n/a; 0.58-0.90	^a^T1-RC, 12, 24, 36, 48
HIV stigma/disclosure	CASAH Social Disclosure Interview [165], Social impact scale [166]		^a^T1-RC, 12, 24, 36, 48
Cognitive function	Peabody Picture Vocabulary Test (PPVT) [167], Symbol Digit Modalities Test (SDMT) [168], Color Trails Test [169], WHO_UCLA Auditory Verbal Learning Test [170], Grooved Pegboard Test [171]	0.61-0.88, 0.76, 0.64-0.79, 0.66, 0.85-0.91	^a^T1-RC, 12, 24, 36, 48
